### Recruitment

All eligible children aged 6–12 years in the participating GP practices will be invited to participate. Eligible patients will be selected by searching the electronic patient database of the GPs and applying the inclusion/exclusion criteria. Parents will be asked to return a response form.

### Study procedures (cluster randomised group)

A researcher (nurse or medical student) will telephone the parents to check whether the children are eligible. Parents will receive the patient information letter with the informed consent form by regular post. When the patient and parents are willing to participate, the informed consent will be signed by the parents/legal guardians and sent to the department of General Practice by post. After all the parents of eligible children of one cluster (who are willing to participate) have provided informed consent, the randomisation is conducted by a researcher and the parents are informed (by telephone) in which treatment arm their child is allocated. Children who turn 12 years during the trial also have to give informed consent. The deadline for randomisation is 8 weeks after inclusion of the first patient of a cluster. Figure 3 is a flowchart of the study procedures.

**Figure 3 F3:**
[figure not shown]
Flowchart of study procedures. PIF, patient information file.

### Study procedures (non-randomised group)

Besides the cluster randomised group of children we will include a non-randomised group of children in this trial. These children will be recruited in health centres who intend to start protocolled nurse-led care for children with asthma in their practice. Practice nurses of the non-randomised participating GP practices will attend the same training on protocolled asthma care. All eligible children who receive protocolled nurse-led care will be invited to participate in the non-randomised part of this trial. They will be invited by their GP with a slightly adjusted invitation letter, the other study procedures will be identical.

## Data collection

### Spirometry

A spirometry test will be conducted at the children’s homes at baseline and at 18-month follow-up using a portable device (CareFusion Vyntus Spiro with SentrySuite Software V.2.21). The spirometry will be conducted by two specialised nurses to minimise interobserver bias and will be performed according to the guideline of the Dutch College of General Practitioners.^6^ The nurses who conduct the spirometry tests will not participate in the protocolled care; they will be appointed as independent research employees. Reversibility will be determined by administering salbutamol via an aerochamber. After the spirometry, the nurse will determine whether the test was properly conducted. Second, the predicted value of FEV1 for age, height and gender will be calculated by a tool of the European Respiratory Society. A score of −2 (SD) is considered as deviant. If the result of the spirometry indicates less than or equal to −2 SD of FEV1 and the child or parents report symptoms such as wheezing or shortness of breath, the nurse advises parents to inform the GP of the child about the current status of the child. In all other cases, to prevent bias, neither the GP nor the parents or the child will be informed about the test result.

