In the present study, two spirometry tests will be conducted. Reversibility will be tested by administering the SABA ‘salbutamol’ (inhalation medication). The dosage of salbutamol will be according to the guideline of the Dutch College of General Practitioners.^6^ Possible side effects include tremor of the hands, headache, peripheral vasodilatation and an increase of heart rate.^6^ However, generally, these symptoms only occur when salbutamol is used in a higher dosage. In this proposed trial, the maximum dosage will never be exceeded. Also, the parents of the child will be asked to cease use of airway dilators before the test; this could lead to a temporary increase of the symptoms of asthma. However, this is a standard procedure for spirometry^6^ and, of course, when it is not possible or medically irresponsible to stop inhalation medication at that moment, spirometry will be postponed.

The participating child, parents, practice nurse and GP will be informed about the results of the spirometry only when the FEV1 is less than or equal to −2 SD of predicted value for age, height and gender. In this case of severe obstruction of the lungs, it would be unethical not to inform them and provide the GP the opportunity to improve the medical condition of the child. If the results are shared in other cases, there is a risk of increased healthcare consumption because of more awareness of the condition or worries of the parents or GP. This could result in bias, because extra review visits (especially in the usual care arm) could be planned, which could lead to better asthma control.

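### The Spirometry section and the Discussion give incompatible rules for disclosing a low FEV1, so a child at or below −2 SD without reported symptoms is withheld under one and disclosed under the other

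*Protocol article*

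**What the plan says.** Spirometry is done at the child's home at baseline and at 18 months by two specialised nurses who take no part in the protocolled care (Protocol article, Data collection, Spirometry). What happens to the result is described in two places.

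**Spirometry section.** The trigger has two parts joined by a conjunction: a result "less than or equal to −2 SD of FEV1 and the child or parents report symptoms such as wheezing or shortness of breath". The action is that "the nurse advises parents to inform the GP of the child about the current status of the child". For everyone else: "In all other cases, to prevent bias, neither the GP nor the parents or the child will be informed about the test result".

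**Discussion, paragraph on the two spirometry tests.** The recipients are listed first: "The participating child, parents, practice nurse and GP will be informed about the results of the spirometry". The trigger is FEV1 alone: they "will be informed about the results of the spirometry only when the FEV1 is less than or equal to −2 SD of predicted value". The reason follows directly: "In this case of severe obstruction of the lungs, it would be unethical not to inform them", so that the GP can act on the result.

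Neither place refers to the other, and neither limits itself to one visit, one arm or one part of the study. The Design section says that study procedures in the non-randomised group are the same apart from randomisation, so the conflict carries over to that group.

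**The concern.** The research nurses need one instruction for a child whose FEV1 is at or below −2 SD. As written, what they should do for a child without reported symptoms depends on which part of the article they follow. The withholding that the Spirometry section prescribes for that child is what the Discussion describes as unethical.

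Two things are at stake. The first is safety: whether an abnormal lung-function result reaches the people who look after the child. The second is consistency: with two rules on paper, similar children may be handled differently between nurses, visits or practices, and nobody could later say which rule had been applied.

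**Working it through.** No figure in the plan depends on this rule, so there is no stated number to reproduce. The check is a comparison of the two rules over the four combinations of FEV1 and symptoms.

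| FEV1 | Symptoms reported | Spirometry section | Discussion | Result |
|---|---|---|---|---|
| At or below −2 SD | Yes | Parents advised to tell the GP about the child's present state | Child, parents, practice nurse and GP informed of the results | Acted on under both; route, content and one recipient differ |
| At or below −2 SD | No | Withheld from GP, parents and child | Child, parents, practice nurse and GP informed of the results | Direct contradiction |
| Above −2 SD | Yes | Withheld | Withheld | Agree |
| Above −2 SD | No | Withheld | Withheld | Agree |

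The rules conflict on the trigger in one of the four combinations, and on detail in another.

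**How many children are affected.** The document gives neither the share of children at or below −2 SD nor the share of those without symptoms. The only available anchor is an assumption, namely that FEV1 scores follow a normal reference distribution:

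- Φ(−2) = 0.0228
- 0.0228 × 180 planned children = 4.1 children at baseline

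This counts every child at or below −2 SD, with or without symptoms. The contradiction concerns only those without, so under this assumption 4.1 is a ceiling and not the size of the conflict. The true share in children with asthma is not given and could differ.

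**Could it move the primary outcome?** An illustration deliberately set to give a large effect:

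- Half of 180 is 90 children per arm, and 0.0228 × 90 = 2.05, so about 2 usual-care children.
- Suppose both are in the disputed group, both are disclosed at baseline, no such child is disclosed in the other arm, and each gains the full 2 C-ACT points that the Sample size section uses as the minimally important difference.
- Shift in the arm mean = 2 × 2 / 90 = 0.04 points.
- With an assumed 10% at or below −2 SD, all of them disputed: 9 × 2 / 90 = 0.2 points.

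Both are small beside the difference of 2 and the SD of 4.1 used in the Sample size section. The 18-month test falls at the same time point as the last C-ACT, so disclosure then can hardly affect the outcome. Only the baseline round could.

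**The case against.** **The wording of the Discussion may state only a necessary condition.** On this reading FEV1 at or below −2 SD is required, and the symptom condition of the Spirometry section is tacitly added. The sentence alone would allow that. The next one does not: it refers back to the threshold alone, calls it severe obstruction and says that "it would be unethical not to inform them and provide the GP the opportunity to improve the medical condition of the child". The other cases are then contrasted with that threshold only. The reading fails.

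**A Discussion paragraph is not an operating instruction, and an article condenses.** Nothing has been left out here. Both rules are given in full, and the Discussion is worded as procedure. If the Spirometry section governs, the ethical justification in the Discussion misdescribes what is done.

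**The difference in recipients is minor.** This largely stands. The Discussion names no messenger, so parents advised at the visit who then tell the GP could satisfy much of it. What remains is that the Discussion adds the practice nurse, and speaks of the results where the Spirometry section has the parents pass on the child's current state.

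**A reader might infer a route to bias in the primary outcome.** The document does mention bias. But the Discussion's remark about extra review visits, especially in usual care, concerns sharing results in cases other than FEV1 at or below −2 SD. The Spirometry section withholds results to prevent bias, which does cover the disputed child, yet nothing indicates that either rule would be applied differently by arm: the spirometry nurses are independent of the protocolled care and neither rule mentions allocation. The illustrative shifts are small as well, and children without reported symptoms plausibly have less room to improve on a symptom score. This objection stands.

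**Conclusion.** The two statements contradict each other on the trigger for disclosure and should not both remain. The contradiction is confined to children with FEV1 at or below −2 SD and no reported symptoms. There is a lesser mismatch in route, content and the naming of the practice nurse for those with symptoms. The conclusion rests on the wording alone and needs no numerical assumption.

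The number of children affected cannot be derived from the document and may be small. The 4.1 of 180 should not be quoted as that number, since it rests on an assumed reference distribution and includes children with symptoms.

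The point matters for participant safety and consistent conduct. It should not be read as showing material bias in average C-ACT: uneven handling by arm is not shown, and the illustrations give 0.04 to 0.2 points under assumptions chosen to enlarge the effect. Which of the two rules is right is a clinical and ethical decision on which this review takes no view.

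**What to change.** Reconcile the two passages into one rule, worded identically in the Spirometry section and the Discussion, that settles:

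- the trigger, including whether reported symptoms are required;
- the recipients, including whether the practice nurse is one;
- the route and content: who tells whom, and whether the spirometry result itself is passed on.

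The clinical leads should decide this with the ethics committee. The nurses' instructions should then be checked against the agreed text.

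Log each baseline disclosure with its date so that counts can be reported by arm. That is enough to show whether the rule was applied evenly.

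Repeating the primary analysis without the disclosed children is not recommended. It would select on an event after enrolment, depart from the intention-to-treat principle in the Analyses section and, with so few children likely to be involved, tell the reader almost nothing.

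The cost is a wording alignment, one log field and possibly a note to the ethics committee. Sample size and planned analyses are unaffected.

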### Baseline measurements and questionnaires

Height and weight, asthma, control according to GINA guidelines, ethnicity of the child, smoking status of the parents and smoking status of the mother during pregnancy will be determined during the baseline visit by the practice nurse. All these items are entered in an online data management system with a secured ‘cloud’ (Research Manager, Deventer, the Netherlands).

The other questionnaires: the C-ACT, CHU9D, EQ-5D-Y, the questionnaire on satisfaction with delivered care, the questionnaire on the frequency/severity of exacerbations and on healthcare costs will be sent to the parents (digitally) at baseline and at 3, 6, 12 and 18 months. The PAQLQ questionnaire will be sent to the parents only at baseline and at 6 and 18 months.

### Retrospective chart review

Direct and indirect healthcare costs and information on co-morbidity will be assessed at 18 months by retrospective chart review. In the Netherlands, all hospital visits (both emergency room visits and cases that are admitted to stay in hospital) are reported to the GP; this includes the duration of stay. The following items will be assessed: referrals from primary to secondary care, number of hospital admissions, medication costs, number and duration of consultations and consultations with the practice nurse and/or the physician (for asthma and non-asthma related symptoms), evidence of stepping-down therapy (ie, reduction in prescribed medication) and information on allergies.

### Withdrawal of individual participants

Participants can leave the study at any time for any reason if they wish to do so, without any consequences. The investigator can decide to withdraw an individual from the study for any urgent medical reasons.

### Analyses

The results of spirometry, the questionnaires and data from the retrospective chart review will be entered in an online and secured data management system (Research Manager). After merging these files, the data will be processed with IBM SPSS for Windows software.

Baseline characteristics will be summarised using simple descriptive statistics. All analyses will be performed according to the intention-to-treat principle. A per-protocol analysis will also be conducted in patients with a maximum ‘no show’ percentage of 33% (1/3 of the review visits).

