### Protocolled care and review visits

A recent qualitative study demonstrated that there is a need for an intervention to help parents optimise the management of childhood asthma.^14^ Research among children from primary and secondary care diagnosed with moderately severe asthma and treated with ICS showed impaired asthma control at 1-year follow-up and less planned review visits for the children in general practice, as compared with children who were treated in secondary care.^15^

Protocolled care by the GP may lead to better asthma treatment in children. Moreover, it seems to be feasible, since two widely supported evidence-based guidelines are available in the Netherlands for asthma care in children in primary care: (1) the GP guideline for asthma in children developed by the Dutch College of General Practitioners in 2014, which provides guidance for diagnosis and management of (suspected) asthma in children^6^ and (2) the care guideline for asthma in children developed by the ‘Lung Alliance Netherlands’ in 2012.^16^ These two guidelines recommend planned reconsultations with structured evaluation of individual care plans and gained goals, allowing to make alterations in the management of the child’s asthma more proactively. Unfortunately, in the Netherlands, regular follow-up of children with asthma, as prescribed in these guidelines, is poorly implemented.^12^

International guidelines promote both a policy of optimal symptom control and a focus on prevention of symptom worsening in the subsequent months (‘risk factors for poor outcome’).^17^ With regard to asthma, a systematic review found no significant difference between hospital-based nurse-led care for patients with asthma compared with physician-led care.^18^ However, the review included a relatively small number of studies and further research was recommended. Moreover, only two relatively small studies of the (in total) five included studies concerned asthma in children and both of these studies evaluated care by hospital-based specialised asthma nurses; therefore, extrapolation of the results to primary care is insufficiently supported.^19 20^

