### Follow-up visits in the intervention group (both randomised and non-randomised)

At baseline and at each control visit, asthma control will be determined by the practice nurse using a four-item questionnaire based on the Global Initiative for Asthma (GINA) guidelines.^17^

The content and frequency of follow-up visits will depend on the asthma control and medication use.

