### Follow-up schedule for well-controlled patients in the intervention group

For well-controlled patients (based on GINA criteria) with asthma diagnosed in the previous year, control visits will be planned according to the medication used. For ‘as needed’ use of SABA, visits will be once in the first 3–6 months. When a patient is well controlled and with asthma diagnosis of >1 year, the control visit will be scheduled annually. When ICS dosage reduction in well-controlled patients is attempted (after 1 year of well-controlled asthma), control visits will be scheduled once every 3 months; at the lowest effective dose once every 3–6 months, and after 1 year, annually.

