### Follow-up schedule for the control group

The content and frequency of the control visits for the control group (‘usual care’) will be determined according to the discretion of the GP.

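### The per-protocol rule (at most one third of review visits missed) has no protocol-defined denominator in usual care and a control-dependent one in the intervention arm, so it should not support a between-arm estimate

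*Protocol article*

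**What the plan says.** The Analyses section makes intention to treat the governing principle: "All analyses will be performed according to the intention-to-treat principle". It then adds a second analysis: "A per-protocol analysis will also be conducted in patients with a maximum" no-show "percentage of 33% (1/3 of the review visits"). One cut-off is given for everyone, with no separate rule for each arm.

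The two arms do not share a visit schedule. For usual care, the section on the control group's follow-up says that the content and frequency of visits "will be determined according to the discretion of the GP". For nurse-led care, "The content and frequency of follow-up visits will depend on the asthma control and medication use". The schedules that follow range widely. For a well-controlled child diagnosed more than a year ago, "the control visit will be scheduled annually". A child who is not controlled on less than optimal medication is seen every 2–4 weeks. A child who continues inhaled corticosteroids is seen every 3 months in the first year.

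**The concern.** A no-show percentage needs a count of planned visits. In usual care the protocol fixes no such count, and the introduction says of Dutch practice that "regular follow-up of children with asthma, as prescribed in these guidelines, is poorly implemented", so some control children may have no planned review at all. In the intervention arm the count exists, but it is driven by asthma control, the construct that the C-ACT measures. Entry to the set then depends on a post-randomisation variable linked to the outcome, and the dependence differs between arms.

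At stake is the meaning of the per-protocol contrast. It would set attenders in one arm against a control group that is unselected or selected on another basis. If the primary model is refitted in this set, its premise that any baseline C-ACT difference is due to chance no longer has randomisation behind it.

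**Working it through.** **Inputs from the protocol.** The cut-off is one third of review visits (Analyses). The schedules are as described above; annual review means about 1–2 visits in 18 months. The MID is 2 C-ACT points (Sample size). The protocol gives no expected no-show rate and no size for the per-protocol set, so there is no figure of its own to reproduce.

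**Assumptions.** No-show probability q of 10–40% per visit, independent between visits. Nine planned visits for a child who is not well controlled. Half the children in each state, with a 4-point C-ACT gap between the two groups. No true treatment effect. The rule removes children from the intervention arm only.

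**Step 1: usual care.** With zero planned visits the ratio is 0/0. If such children are kept, selection falls mainly on the intervention arm. If they are dropped, the control arm shrinks to children whose GP chose to plan reviews. Neither reading is the randomised comparison.

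**Step 2: chance of entering the set in the intervention arm.** With n planned visits, at most floor(n/3) may be missed, so P(enter) = sum over k = 0 to floor(n/3) of C(n,k) q^k (1-q)^(n-k).

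| Planned visits | Misses allowed | q = 10% | q = 20% | q = 30% |
|---|---|---|---|---|
| 1 | 0 | 0.90 | 0.80 | 0.70 |
| 2 | 0 | 0.81 | 0.64 | 0.49 |
| 3 | 1 | 0.972 | 0.896 | 0.784 |
| 5 | 1 | 0.919 | 0.737 | 0.528 |
| 8 | 2 | 0.962 | 0.797 | 0.552 |
| 9 | 3 | 0.992 | 0.914 | 0.730 |

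The same attendance behaviour gives different chances of entry, and the chance does not rise steadily with the number of visits.

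**Step 3: spurious difference with no true effect.** Well-controlled children lie 2 points above the arm mean and the others 2 points below. With entry probabilities w and u, the retained mean differs from the full-arm mean by 2(w - u)/(w + u).

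- Equal q = 20%, 1 v 9 visits: 2(0.800 - 0.914)/1.714 = -0.13.
- Equal q = 20%, 2 v 9 visits: 2(0.640 - 0.914)/1.554 = -0.35.
- Equal q = 30%, 1 v 9 visits: 2(0.700 - 0.730)/1.430 = -0.04.
- Equal q = 30%, 2 v 9 visits: 2(0.490 - 0.730)/1.220 = -0.39.
- Poorly controlled children miss more (10% v 30%), 2 v 9 visits: 2(0.810 - 0.730)/1.540 = +0.10.
- Poorly controlled children miss more (10% v 40%), 2 v 9 visits: 2(0.810 - 0.483)/1.293 = +0.51.
- Well-controlled children miss more (30% v 10%), 1 v 9 visits: 2(0.700 - 0.992)/1.692 = -0.35.
- Equal q = 30%, but 1 v 8 visits: 2(0.700 - 0.552)/1.252 = +0.24.

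The last line shows that changing nine planned visits to eight can reverse the sign even when no-show rates are equal. A simulation of the first seven cases agreed with the formula to within 0.01. The shift is proportional to the assumed gap, so a 2-point gap would halve every figure.

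**Step 4: the planned model.** These are unadjusted differences in means. The primary model includes baseline C-ACT, which removes part of a difference already present at baseline. With a stable gap, equal variances and an assumed baseline-to-follow-up correlation of 0.5, the shift is multiplied by 1 - 0.5. Then +0.51 becomes about +0.26 and -0.39 about -0.20. Selection on control that changes after baseline is not removed in this way.

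**The case against.** The strongest reply is that this is an additional analysis in a condensed article. Intention to treat governs, no stated conclusion rests on the per-protocol set, and handling of children with no planned visit could sit in a fuller document. That limits the weight of the point but does not answer it: the numerical rule is stated here, and it is unsuitable for comparing the arms as it stands. Selection after randomisation is also a general weakness of per-protocol analyses; what is particular here is a denominator that exists by protocol in one arm only and moves with asthma control.

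A reader might infer that the rule cannot be applied in usual care at all. The text does not support that. The control-group section presupposes that visits occur, and the Discussion says that "extra review visits (especially in the usual care arm) could be planned". A ratio can be formed for some control children, though not on an equal footing.

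A reader might also infer that the bias must favour nurse-led care because good attenders tend to do better. If a share p is excluded and scores d points below those retained, the retained mean is too high by p × d: 0.25 × 2 = 0.5, or 0.1 (0.10 × 1) to 0.9 (0.30 × 3). That is only one of the two mechanisms. Easy exclusion of well-controlled children with one or two visits works the other way, and nothing in the document says which prevails.

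**Conclusion.** The point holds for the per-protocol comparison between arms. The rule lacks a protocol-defined denominator in usual care, and in the intervention arm the denominator follows control and medication. The resulting contrast is not randomised and its bias has no known sign. The illustrations run from about -0.4 to +0.5 C-ACT points before baseline adjustment, well below the MID of 2. They rest on assumed no-show rates, visit counts, a 4-point gap and a half-and-half split, none of which the protocol gives.

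The primary intention-to-treat result is not affected, and the document gives no ground for reading this as a threat to it. The risk is that a per-protocol estimate of unknown bias is taken to confirm or to weaken that result.

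**What to change.** State in the Analyses section that intention to treat is the only basis for between-arm inference, and that attendance at review visits will be described within the intervention arm only. This costs a sentence or two and changes no visit schedule.

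If an adherence-adjusted effect is wanted, specify before outcome data are seen an instrumental-variable (complier-average) analysis as follows:

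- Keep all children in the randomised clusters, leave out the non-randomised sample, and use cluster allocation as the instrument.
- Define uptake as any protocolled nurse-led visit attended. A two-thirds cut-off would bring back the control-dependent ratio and treat partial attenders, who receive some of the education and care planning, as unexposed. The proportion attended can serve as a sensitivity measure, with the caveat that it shares that denominator.
- Measure nurse-led uptake in usual care. The protocol does not bar nurse contacts there, so zero uptake should not be assumed. The chart review already lists practice-nurse consultations; asthma review visits would need to be marked.
- Use cluster-level inference with a small-sample correction, since the Setting section names 13 centres and at least 14 smaller practices, some of which may be merged into one cluster.

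The cost is one paragraph, one extra model and a wider interval than the naive per-protocol one. The analysis also assumes that allocation does not affect children whose uptake it leaves unchanged, and this should be stated.
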